**Figure 1. F1:**
[figure not shown]
Study flowchart. ESM: experience sampling method.

#### Key Stakeholder Interviews

Qualitative material will be collected from semistructured in-depth interviews with adolescents, their parents or legal guardians, and school professionals after adolescents have completed the intervention period. Interviews will be conducted at each pilot site, either in person or online. Clinicians will be interviewed specifically on the topic of the SMILE DSS as part of the SMILE tools. The interview guides are presented in Multimedia Appendix 1.

### Inclusion and Exclusion Criteria

#### Proof-of-Concept Study

Participants are adolescents and young adults aged 10‐24 years who meet the following inclusion criteria: (1) provision of informed consent (participants aged <16 years in the United Kingdom, <15 years in Slovenia, and <18 years in all other pilot sites require consent from a parent or legal guardian in addition to their own assent); (2) completion of measures assessing the primary outcomes; and (3) normal or corrected-to-normal vision. Participants are excluded if they are unable to provide informed consent or if they report a current confirmed diagnosis or ongoing treatment for any of the following conditions: (1) a severe mental disorder (eg, schizophrenia, bipolar disorder, or severe depression); (2) a substance use disorder; (3) epilepsy; or (4) gaming addiction. At the University of Edinburgh site, participants were not excluded based on current mental health diagnosis or treatment status, in line with local ethical guidance. No restrictions are placed on concomitant care. The study does not monitor, regulate, or influence participants’ use of additional support, services, or interventions during the trial.

#### Key Stakeholder Interviews

For parents or legal guardians, eligibility requires having a child in their care who has completed participation in the active phase of the intervention (ie, finished playing the game). School professionals and mental health clinicians are eligible if they are currently working with adolescents and young adults aged 10‐24 years. Adolescents and young adults are eligible to participate after completing the game. No exclusion criteria apply.

### Participant Recruitment and Procedure

#### Proof-of-Concept Study

Each of the 7 participating sites implemented its own recruitment strategy while adhering to shared guidelines. Participants are recruited primarily through schools and universities, with additional outreach via private networks, social media, and community channels. Clusters are defined at the level of the recruitment setting. In most cases, a cluster corresponds to a single school or university. In addition, some “open clusters” were formed by grouping adolescents or young adults recruited from multiple sources (eg, via social media advertisements). Within each cluster, participants are enrolled up to a predetermined size, typically comprising 40‐60 individuals. Adolescents, young adults, and, where applicable, their legal guardians receive an information sheet and provide informed consent prior to participation. Eligibility is then assessed according to predefined inclusion and exclusion criteria, and eligible individuals are enrolled in the study. Before the intervention begins, participants receive onboarding materials with instructions for downloading and setting up the study apps. Depending on the site, onboarding is conducted either remotely or during a brief in-person session. At the start of the study, participants are provided with login credentials and instructions for initiating gameplay. Participation in the trial is fully remote. Participants engage with both the SMILE Game App and the SMILE Companion App at their own pace and at times convenient to them, with occasional check-ins from the research teams.

#### Key Stakeholder Interviews

During recruitment for the proof-of-concept study, participants are asked whether they would be willing to take part in a follow-up interview after completing the game; this invitation is repeated at the end of the intervention. From those who express interest, 10 adolescents per site are randomly selected and invited to participate in individual interviews. Parents or legal guardians are similarly invited following their child’s completion of the game, with 10 selected per site from those who indicate willingness to participate. Teachers from participating schools or colleges are also invited, and 5 school professionals per site are randomly selected. Where appropriate, up to 5 child and adolescent mental health professionals per site are recruited through local services, professional networks, and targeted outreach (eg, social and traditional media). Interested clinicians are contacted by the research team, provided with study information, and screened for eligibility prior to participation. Semistructured interviews are conducted after adolescents have completed the intervention. Interviews take place at each pilot site, either in person or online, and are scheduled only after participants in a given sequence have completed the game. Each interview lasts approximately 30‐60 minutes. All participants provide informed consent prior to participation.

### Sample

#### Proof-of-Concept Study

The trial will be conducted among clusters of adolescents and young adults, aged 10 to 24 years who fulfill the inclusion criteria. The sample size calculation was specified a priori assuming 3 sequences with 4 clusters per sequence. Because the sample size calculation, conducted with the Shiny CRT Calculator [54], permitted specification of only a single intervention condition, the sample size estimate was doubled to reflect the trial’s intervention structure. The calculation assumed an error level of α=.05, power of 1–β=0.80. Clustering was modeled with an intracluster correlation (ICC) of 0.01 [55,56], and within-participant autocorrelation was set to 0.60 [57]. A standardized effect size of 0.20 was assumed for all primary outcomes. Since the sample is considered to derive from a healthy population, changes in depression and anxiety symptoms were expected to be small. Applying the same effect size across outcomes provided a consistent basis for sample size estimation and represented the smallest effect of interest. Given the exploratory nature of the study, no formal alpha adjustment was applied. A dropout rate of 50% was assumed. Under these assumptions, 24 participants per arm per site are required, corresponding to 992 participants overall. On top of the included dropout expectations, to account for attrition reported in comparable trials (24%‐83%) [58,59], the recruitment target was increased to 1438 participants.

Because the trial follows an adaptive design with 2 interim analyses, the initial sample size estimate will be treated as provisional. Interim data will be used to update key parameters and adjust sample size for subsequent stages as needed. This approach will enable us to gather sufficient data to inform potential subsequent definitive randomized controlled trials and to refine the intervention as necessary.

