The intervention is rolled out over a 10-month period from September 2025 to June 2026. Three sequences are planned, separated by 3-week intervals; however, the length of the interval may vary depending on any implemented modifications. Clusters are allocated to sequences based on site-specific feasibility and readiness, meaning that clusters enter the rollout at different points depending on when they are prepared to initiate the intervention. Consequently, the number of clusters varies across sequences. In total, 46 clusters across 7 pilot sites will be included in the rollout. Each game module is designed to last no longer than 20 minutes. With 5 modules in total, including all study measures, participants are expected to spend a maximum of approximately 4.5 hours on the study, distributed over several weeks.

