### Other Measures

In addition to the primary and secondary outcomes, we will assess feasibility and acceptability outcomes, user data, in-game metrics, and diary recordings.

Feasibility and acceptability outcomes will include (1) cluster recruitment yield, defined as the proportion of clusters included relative to the total number of clusters invited, with a predefined success criterion of at least 80%; (2) uptake, defined as the proportion of participants who completed the minimum intervention dose (defined as completing baseline measurement and at least one game module) relative to all included participants, with a predefined success criterion of at least 66%; (3) engagement with the SMILE serious game based on in-game measures (Table 1); (4) adherence, operationalized as the average proportion of completed game modules relative to the total of 5 modules, with a predefined success criterion of at least 50%; (5) dropout, defined as the proportion of participants who disengaged from the study at any point between baseline and posttest relative to all participants, with a predefined criterion of less than 45%; (6) adverse events, assessed and summarized.

We will also collect user data restricted to the study apps (ie, the Game App and Companion App). User data will include app usage frequency; drop-off points (where users typically stop using the app); session duration; session start and end times; whether sessions are completed with or without interruptions; completion rates; frequency of engagement with the game; and the average time spent per session.

During SMILE gameplay, the Game App will collect various in-game metrics. These include measures of behaviors such as proximity to NPCs, performance in specific tasks, or in-game affect ratings. Table 1 provides a detailed description of these metrics.

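### The stated 24 per arm per site does not give 992, and the sample-size calculation describes about 24 clusters while the trial runs 46

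*Protocol article*

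**What the plan says.** The Sample section (Proof-of-Concept Study) says the calculation was "specified a priori assuming 3 sequences with 4 clusters per sequence". Because the calculator accepted only one intervention condition, the result was doubled. The stated inputs are:

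- "The calculation assumed an error level of α=.05, power of 1–β=0.80"
- "Clustering was modeled with an intracluster correlation (ICC) of 0.01", with a within-participant autocorrelation of 0.60
- "A standardized effect size of 0.20 was assumed for all primary outcomes"
- a dropout rate of 50%

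The result is given as "Under these assumptions, 24 participants per arm per site are required, corresponding to 992 participants overall". The recruitment target is then raised to 1438 for attrition beyond the dropout already included. A literature range of 24% to 83% is cited, but not the rate applied.

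Elsewhere the article describes the trial as it is run. Study Design: "In total, 46 clusters across 7 pilot sites will be included in the rollout". Results confirms that 46 clusters had been recruited by March 2026. Participant Recruitment and Procedure: "Within each cluster, participants are enrolled up to a predetermined size, typically comprising" 40 to 60 people. The Randomization section has two allocations, feedback and no feedback. The Data Analysis Plan lists three conditions, the third being the baseline control.

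**The concern.** Two things do not fit. First, the sentence that links the per-arm, per-site number to the total does not follow from the arms and sites that the article describes. Second, the calculation belongs to a design with about half as many clusters as the trial has, and the quoted cluster size appears to be left over from that design.

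The 80% power claim and the 992 and 1438 targets are the article's only justification for the size of the trial. The interim analyses are meant to update this calculation, and the results are meant to inform a definitive trial. As written, a reader cannot tell which arms, how many clusters or what attrition the 80% refers to. Nor can a reader see how precisely the trial will estimate the feedback versus no-feedback difference, which is its only randomised contrast.

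**Working it through.** **1. From 24 per arm per site to 992.** Inputs: 24 per arm per site and 50% dropout (Sample), 7 sites (Study Design), 2 randomised variants (Randomization).

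- Two arms: 24 × 2 × 7 = 336; with dropout, 336 / 0.5 = 672.
- Three conditions, counting the control period: 24 × 3 × 7 = 504; 504 / 0.5 = 1008. This is 1.6% above 992, and working back, 992 × 0.5 / 21 = 23.6, which rounds up to 24.
- 24 read as evaluable participants per cluster in 24 clusters: 24 × 24 / 0.5 = 1152.

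None gives 992. The three-condition reading is nearest, but the control condition is a period in the same participants, not a separate arm. It also multiplies by three, where the text says the estimate was doubled.

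**2. Clusters.** 3 × 4 = 12, doubled = 24 (an inference, since the text says the estimate was doubled).

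| | 24 clusters | 46 clusters |
|---|---|---|
| 992 enrolled | 41.3 each | 21.6 each |
| 1438 enrolled | 59.9 each | 31.3 each |

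The 40 to 60 range matches the 24-cluster column almost exactly. At 46 clusters, 40 to 60 each would be 1,840 to 2,760 people.

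**3. From 992 to 1438.** 1438 / 992 = 1.45. Read as a loss, 1 − 992 / 1438 = 31%. Taken with the 50% inside 992, the evaluable number is 496, and 1 − 496 / 1438 = 65.5% total loss.

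**4. Does this show low power?** The article does not state the number of periods, the cluster autocorrelation (CAC) or the sidedness. Assumed here: a closed-cohort stepped wedge, 4 periods, two-sided test, CAC 0.8 to 1. For m evaluable per cluster and ICC ρ = 0.01, cluster-period means have variance ρ + (1 − ρ)/m and between-period covariance ρ × CAC + 0.60(1 − ρ)/m. The effect variance is the generalised-least-squares variance with fixed period effects, and power = Φ(0.20/SE − 1.96).

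- 12 clusters (one variant), 80% power: m = 22 (CAC 1), 24 (CAC 0.9), 25 (CAC 0.8). Doubled and with 50% dropout, m × 24 / 0.5 gives 1,056 to 1,200 enrolled.
- At 992: m = 496 / 24 = 20.7, power 74% to 78%.
- At 1438 with 50% dropout: m = 719 / 24 = 30.0, power 86.5% to 90.5%.
- 46 clusters spread evenly over 3 sequences, both variants pooled against control, 50% dropout: about 97% at 992 and above 99% at 1438. This is idealised, because actual clusters per sequence are not given.

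**5. Feedback versus no feedback.** Assume k = 23 clusters per variant, one baseline and one post measure, and d = 0.20. With v and c the variance and covariance from step 4 and r = c/v, the variance of the adjusted difference is 2v(1 − r²)/k. At 1438 with 50% dropout, m = 719 / 46 = 15.6. For CAC 1:

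- v = 0.0733, c = 0.0480, r = 0.655
- variance = 0.00364, SE = 0.060
- 95% half-width 0.12 SD, power 91%

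Over CAC 0.8 to 1:

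| Clusters | 992 enrolled | 1438 enrolled |
|---|---|---|
| 46 | 77% to 79% | 90% to 91% |
| 24 | 75% to 78% | 87% to 91% |

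More, smaller clusters at the same total therefore do not cost power.

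**The case against.** The best defence has four parts.

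- **Near reproduction.** Three conditions give 1008, and 23.6 rounds up to 24. The article never defines an arm, and the calculator settings may sit in a fuller document. This stands far enough that nobody can say 992 is irreproducible; it can be neither confirmed nor refuted. It does not rescue the sentence as written.
- **Provisional and adaptive.** The estimate is called provisional, and cluster number and size may change after interim analyses. That explains why 46 may differ from 24. It does not explain an article that reports 46 clusters beside a calculation and a cluster size that fit 24.
- **Cluster size is a ceiling.** The wording is up to a set size, and typically 40 to 60. So an average of 31 is not a strict contradiction, and 1,840 to 2,760 should not be read as an implied target. It still sits badly with a typical size of 40 to 60.
- **Attrition.** A reader might infer double counting, or a conflict with the feasibility criterion (dropout "relative to all participants, with a predefined criterion of less than 45" per cent). Neither holds. The second allowance is openly declared and conservative, the 65.5% total lies inside the cited 24% to 83%, and a success threshold need not equal a planning assumption. What stands is only that the second rate is missing.

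It is also fair to say that feedback versus no feedback carries secondary hypotheses only and that P values are to be read descriptively. Formal power for that contrast is not obligatory, though its precision is worth reporting.

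**Conclusion.** The sample-size statement is inconsistent as written and was not restated for the design being run. On the described arms and sites, 24 per arm per site gives 336 or 672 (1008 on the most generous reading), not 992. The calculation and the cluster size fit 24 clusters, while the trial has 46, at about 31 enrolled each. The 24 is an inference from the doubling.

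A reader might go further and conclude that the trial is underpowered. The documents do not support that. The 74% to 78% at 992 depends on unstated inputs: adding one measurement period to the same model brings it to about 78% to 81%. At the actual target of 1438 with 50% dropout the model gives about 87% to 90%, and the move to 46 clusters does not reduce power. If both attrition allowances were fully used, the evaluable number would return to 496, so the article should say which attrition its power refers to. All power figures here rest on the assumptions in the working (stepped wedge, four periods, CAC 0.8 to 1, two-sided test, equal cluster sizes).

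**What to change.** Rewrite the sample-size paragraph:

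1. Define an arm, correct the statement that equates 24 per arm per site with 992, and show each step to 992 and to 1438 with the attrition rate applied at each.
2. State the unstated inputs: number of periods, cluster autocorrelation, sidedness, and whether the doubling applies to clusters or to participants.
3. Restate power, or the expected confidence-interval half-width, for game versus control period with 46 clusters, about 31 enrolled per cluster and the actual number of clusters in each sequence.
4. Report the precision of the randomised feedback versus no-feedback contrast with baseline adjustment.
5. Reconcile the 40 to 60 cluster size with 46 clusters and 1438 participants.

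The cost is one re-run calculation and one corrected paragraph. No extra enrolment is needed. The only downside is that a published figure may change.

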#### Key Stakeholder Interviews

Semistructured interviews will be conducted with adolescents aged 10‐24 years who completed the SMILE intervention as part of the proof-of-concept study (n=10), as well as parents or legal guardians (n=5‐10), school professionals (n=5‐10), and clinicians (n=5‐10). In total, we intend to interview n=25 per site at a minimum and 40 at a maximum, amounting to 280 participants in total. To determine the sample size, we used the concept of information power [48,49]. We estimated sample size based on (1) the specificity of study aims, (2) the specificity of the study sample, (3) the theoretical background of the study, (4) the quality of the interviews with study participants and, finally, (5) analysis strategy (cross-case vs case), and (6) feasibility, as 4 participant groups will be coordinated in 7 pilots following one interview schedule.

### Randomization: Proof-of-Concept Study

Proof-of-concept study uses a cluster randomized multisite multiarm adaptive trial design, meaning that randomization occurs at the cluster level and involves assigning each cluster to either feedback or no-feedback variant. Randomization is conducted in blocks (using block randomization) at the consortium level using REDCap software (Vanderbilt University) by a statistician who is not involved in the study. Confirmed clusters for the upcoming sequence were randomized and this process was repeated for new clusters before each sequence. Clusters are allocated pragmatically between sites and adjusted in size and distribution if indicated by the adaptive interim analyses. There is no randomization at the individual level. Clusters will be blinded to their allocation (ie, whether they receive the intervention with or without feedback). No unblinding is planned during the trial.

### Measures in the Proof-of-Concept Study

There are 7 types of data that we will collect in this phase. First, there are self-reported primary and secondary measures that will be collected at the following time points (Table 2): baseline (T0; 1 to 2 weeks before the intervention), right before the intervention (T1), during the intervention (T2), and at posttest (T3; after completion of the intervention). Additionally, measures of depression and anxiety (ie, primary outcomes) will be distributed on a weekly basis, alternating between a depression scale 1 week and an anxiety scale the next. Secondary measures (ie, well-being and resilience) will be collected every other week. Second, participants will be invited to respond to a short daily survey using ESM, 5 times a day (Table 3). Third, there will be in-game measures related to the current activity in the game (Table 1). Fourth, we will collect vocal and facial data via weekly diary recordings. Fifth, we will assess the feasibility and acceptability of the game through measures other than participants’ responses. Finally, we will collect user data that are restricted to the SMILE apps: the Game App and the Companion App. All measurements described below will be collected by the SMILE end user apps.

**Table 2. T2:** Study measures and time points.

Variable	T0^a^	T1^b^	T2^c^				T3^d^
	Sequence 1			Sequence 2		Sequence 3	Posttest
	Week 1	Week 2	Week 3	Week 4	Week 5	Week 6	
Anxiety	✓	✓		**✓**		**✓**	**✓**
Depression	✓	✓	**✓**		**✓**		**✓**
Well-being	✓	✓		**✓**		**✓**	**✓**
Resilience	✓	✓		**✓**		**✓**	**✓**
Privacy concerns	✓						
Acceptance (of SMILE^e^ Game App)							**✓**
Acceptance (of SMILE Companion App)							**✓**
User experience (in SMILE Game App)							**✓**
User experience (in SMILE Companion App)							**✓**

a T0=Time 0 (before baseline period).

b T1=Time 1 (before the start of the game).

c T2=Time 2 (during the game period).

d T3=Time 3 (after the intervention).

e SMILE: Supporting Mental Health in Young People: Integrated Methodology for Clinical Decisions and Evidence-Based Interventions.

**Table 3. T3:** Data collected via experience sampling methods.

Variable	Morning	Midday	Midday	Midday	Evening
Sleep quality	✓				
Mood		✓	✓	✓	✓
Location		✓	✓	✓	✓
Activity context		✓	✓	✓	✓
Social context		✓	✓	✓	✓
Stress coping		✓	✓	✓	
Emotion regulation		✓	✓	✓	✓
Reflective functioning					✓
Social anxiety^a^		✓	✓	✓	
Self-efficacy^a^					✓

a Collected only during baseline and then again in weeks 5 and 6.

### Primary Outcomes

Primary outcomes are depression and anxiety. To measure anxiety, we use the Penn-State Worry Questionnaire for Children (PSWQ-C [60]) for participants aged 10‐17 years and the Generalized Anxiety Disorder-7 item (GAD-7 [61]) for participants aged 18‐24 years. To assess depression, we use the Patient Health Questionnaire for Adolescents (PHQ-A; [62]) for participants aged 10‐17 years and the Patient Health Questionnaire-9 item (PHQ-9; [63]) for participants aged 18‐24 years. Completion of primary outcome measures at T0 and T1 is mandatory within the SMILE apps.

### Secondary Outcomes

Main secondary outcomes include self-reported well-being and resilience, assessed with measures appropriate to the age group: the Warwick–Edinburgh Mental Well-being Scale (WEMWBS [64]) for ages 10‐24 years, the Child and Youth Resilience Measure (CYRM-12 [65]) for ages 10‐17 years, and the Brief Resilience Scale (BRS [66]) for ages 18‐24 years. Moreover, we measure online privacy concerns [67], technology acceptance [56], and user experience for both apps using the short User Experience Questionnaire [68]. Completion of secondary outcome questionnaires is optional for participants.

In addition to questionnaire data, selected secondary outcomes will also be derived from daily ESM responses (Table 3).

